#### Statistical analysis

The primary analysis will be performed adhering to the intention-to-treat principle. Descriptive statistics will be used to summarize characteristics of both participants and practices. Since the study has a hierarchical structure in which participants are nested within general practices, we will use hierarchical mixed-effects regression models / multilevel modeling approach to evaluate differences between the intervention and the control group in change in functional abilities between baseline and follow-up as measured with the Katz-15 index and all secondary outcomes. We will correct for the relevant covariates. Furthermore, the effect of the intervention on mortality, and on the time to hospital and nursing home admissions will be analyzed using survival analysis (Kaplan-Meijer curves) and Cox proportional hazard regression models. An additional sensitivity analysis will be conducted on a per-protocol analysis set, and on a subset of general practices in which the intervention is optimally implemented. Interim analyses will not be conducted. Statistical analyses will be performed using SPSS version 20.

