### Cost-effectiveness study

#### Outcome measures and data collection

The primary outcome is the change in the level of functional performance in ADL between baseline and follow-up at twelve months, as measured with the Katz-15 index
[28].

Secondary outcomes are:

1. Quality of life, as measured with RAND-36
[29] and EQ-5D
[30]

2. Psychological and social functioning, as measured with a subscale of the RAND-36
[29]

3. Number of residential home, nursing home and hospital admissions

4. Mortality

Participants’ data are collected at baseline and at follow-up at twelve months with the EasyCare-TOS, in which baseline characteristics, the Katz-15 index, RAND-36, EQ-5D, and data on health service utilization and mortality are embedded.

Caregiver burden is measured with the Carer-Qol
[31], which is embedded in a structured caregiver questionnaire, to be filled in by the main informal caregiver.

Last, regular health care costs and costs of the CareWell-primary care program are collected with the EasyCare-TOS and through external sources, as shown in Table 
1.

**Table 1 T1:** Overview of sources used to obtain regular health care costs and costs of the CareWell-primary care program

**Costs**	**EasyCareTOS**	**External source**

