#### Sample size calculation

The change in functional status between baseline and follow-up will be measured as a change in the sum-score on the Katz-15 index between baseline and 12 months
[28]. Although the Katz-15 index scores may be skewed, we expect these sum-score differences to have a normal distribution. For financial and logistic reasons, including 6 clusters in each study-arm is thought to be feasible. Each general practice is instructed to include 50 frail elderly. Based on the assumptions that 15% of eligible elders will decline informed consent and 20% will be lost to follow-up within the intervention-period of twelve months, the expected cluster size is 35. Using a two-sided alpha of 0,05, a power of 80%, an assumed between-clusters ICC of 0,01
[32], and a minimum cluster size of 35 with 2×6 clusters, we will be able to detect an effect size of >0,32, which is sufficient to detect even small differences
[33,34].

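### The Cox models for mortality and time to admission are named with no provision for practice clustering; run as written at ICC 0.01, a nominal 5% test has a true size of about 9% to 11%

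*Protocol article*

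**What the plan says.** In the protocol article, the Statistical analysis section of the cost-effectiveness study opens the modelling plan with "Since the study has a hierarchical structure in which participants are nested within general practices, we will use hierarchical mixed-effects regression models". It applies these models to change in functional abilities "as measured with the Katz-15 index and all secondary outcomes".

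A separate sentence, introduced as an addition, takes up "the effect of the intervention on mortality, and on the time to hospital and nursing home admissions". These "will be analyzed using survival analysis (Kaplan-Meijer curves) and Cox proportional hazard regression models". No clustering device is named in that sentence.

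The section Outcome measures and data collection lists "Number of residential home, nursing home and hospital admissions" as the third secondary outcome and mortality as the fourth. Time to admission is not on the list. The only software named for these analyses is in the statement "Statistical analyses will be performed using SPSS version 20".

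**The concern.** Arm is allocated to whole practices, six against six. A Cox model or log-rank test that treats participants as independent omits the between-practice part of the variance of the arm comparison. Differences between practices in admitting habits or case mix can then pass for a programme effect. Such differences are plausible here: allocation is non-random, and intervention practices are chosen for motivation and organisational facilities.

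Reducing or postponing hospital and nursing home admissions is a stated aim of the programme, so a falsely precise hazard ratio on admission would carry weight in the report. Mortality has a further difficulty. It is covered by both the multilevel sentence and the Cox sentence, and the article does not say which result governs if they disagree.

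**Working it through.** **1. Reproduce the plan's own figure.** Inputs from Sample size calculation: two-sided alpha 0.05 (z = 1.960), power 80% (z = 0.842), ICC 0.01, 6 practices per arm, m = 35 per practice.

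- Design effect: DE = 1 + (m − 1) × ICC = 1 + 34 × 0.01 = 1.34.
- Detectable effect: d = (1.960 + 0.842) × √(2 × DE / (6m)) = 2.802 × √(2.68 / 210) = 0.317.
- With m = 50 × 0.85 × 0.80 = 34: DE = 1.33 and d = 0.320.
- Without the design effect, at m = 35: 2.802 × √(2 / 210) = 0.273.

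The stated 0.32 is reproduced, and only when clustering is counted.

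**2. Apply the same ICC to an unadjusted survival test.** If the variance leaves out clustering, the null test statistic has variance of about DE instead of 1. Its true size is 2 × (1 − Φ(1.96 / √DE)), and its interval is 1/√DE of the correct width. Two practice sizes bracket the case: 35 (Sample size calculation, after refusal and loss) and 50 (300 per arm over six practices, in the section on study participants). Survival analysis keeps partial follow-up, so the relevant size can exceed 35.

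| m | DE | √DE | 1.96/√DE | True size | Interval too narrow by |
|---|---|---|---|---|---|
| 35 | 1.34 | 1.158 | 1.693 | 9.0% | 1 − 1/1.158 = 14% |
| 50 | 1.49 | 1.221 | 1.606 | 10.8% | 1 − 1/1.221 = 18% |

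A null log-rank simulation agrees (8,000 runs, 12 practices of 50, assumed 30% with an event): rejection was 4.8% at ICC 0 and 10.9% at ICC 0.01.

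**3. Hazard-ratio scale, for illustration.** Assume 60 deaths among 600 participants. The standard error of the log hazard ratio is about 2/√60 = 0.258. The unadjusted 95% limits are the estimate divided and multiplied by exp(1.96 × 0.258) = 1.659. With DE = 1.49 the factor is exp(1.96 × 0.258 × 1.221) = 1.855.

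**4. Range over the ICC.** The article gives no ICC for these outcomes. With m = 50, an assumed ICC of 0.02 gives DE = 1.98 and a size of 16.4%. An assumed 0.05 gives DE = 3.45 and a size of 29.1%.

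**5. Deaths in the time-to-admission analysis.** Assume constant hazards of 0.3 per year for admission and 0.1 per year for death, over one year.

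- One minus Kaplan-Meier with deaths censored: 1 − exp(−0.3) = 25.9%.
- Cumulative incidence: 0.3/0.4 × (1 − exp(−0.4)) = 24.7%.

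The test behaves differently from the curve. In null simulations without clustering (20,000 runs each), censoring at death gave a size of 5.1% with equal death hazards and 5.0% with the death hazard doubled in one arm.

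**The case against.** The strongest reply is that the multilevel commitment covers all secondary outcomes, and that these include mortality and the number of admissions. The Cox sentence only adds to that commitment and never says its models are unclustered. An article may also leave a frailty term to a fuller document. Part of this stands: one cannot conclude that the investigators intend to ignore clustering. But the commitment does not reach time to admission, which appears only in the survival sentence. For mortality it leaves two analyses and no order between them. The method is named, and run as named it treats participants as independent.

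A reader might also infer that deaths will be censored and that this too makes the p-values optimistic. The article does not support that. It does not say how death is handled in the admission analyses, and censoring at death leaves the cause-specific test at about 5%. For mortality, death is the event, so the issue cannot arise. What remains is a modest upward bias in a Kaplan-Meier admission curve if deaths are censored.

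It is also fair to object that the ICC of 0.01 was assumed for the Katz-15 sample size, not for survival outcomes, and that 50 per practice is the upper end of the range. The size is therefore given as a range and as conditional.

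**Conclusion.** The point holds, at moderate severity. As worded, the survival analyses carry no allowance for the nesting that the article itself gives as its reason for multilevel models and counts in its sample size. The true size of a nominal 5% test would be about 9% to 11%, with log-hazard intervals 14% to 18% too narrow. This rests on two conditions: that no adjustment is made, and that the ICC of 0.01 carries over. The 16% and 29% figures rest on ICCs that the article does not give, so they show sensitivity and are not expected values.

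The competing-risk point is separate and smaller. It affects the displayed admission probability (25.9% against 24.7% under assumed hazards), not the error rate. Only secondary analyses are involved; the primary Katz-15 analysis is explicitly multilevel and is untouched.

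**What to change.** State in the Statistical analysis section that the Cox models for mortality and time to admission include a shared frailty for general practice. Alternatively, specify a practice-level cluster-robust variance with a small-sample correction and a t reference on about 12 − 2 = 10 degrees of freedom. State which mortality analysis governs, the multilevel model or the Cox model. Confirm that the named package can fit the chosen method, and name another if it cannot.

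For time to hospital and nursing home admission, show cumulative incidence curves with death as a competing event. The Cox model can remain as a cause-specific hazard analysis.

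The cost is wording, possibly a second software routine, and precision; no new data are needed. At ICC 0.01 the log-hazard intervals become about 16% to 22% wider than unadjusted ones (√1.34 = 1.158; √1.49 = 1.221). With the t reference the factor is multiplied by 2.228/1.960 = 1.137, giving about 32% to 39%. The change corrects the variance only. It does not remove bias from the non-random allocation of practices.

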#### Economic evaluation

The economic evaluation will be conducted from a societal perspective. All relevant direct and indirect costs per participant will be determined by considering costs of the CareWell-primary care program, for the intervention group, and regular health care costs, for both the intervention and the control group. The costs of the CareWell-primary care program will be calculated from the registrations of health care professionals of the time spent on the elements of the program. Regular health care costs will be collected with EasyCare-TOS and external sources, as shown in Table 
1.

Unit resource prices are based on guideline prices according to the Dutch Insurance Board
[35]. Real costs prices will be determined when unit resource prices are not available. Societal costs are quantified by calculating productivity losses for informal caregivers who perform paid labor during the study period using the friction cost method
[36]. Data on productivity losses will be obtained using the structured caregiver questionnaires.

The incremental cost-effectiveness ratio (ICER) will be expressed as costs per quality-adjusted life years (QALYs) gained, as measured with the Euroqol-5D
[30]. From these EQ-5D scores, utilities will be derived using the trapezium rule and the Dutch algorithm after which QALYs will be calculated
[37].

Next to this, the ICER will be expressed as the difference in total mean costs weighed against the difference in the sum-scores between baseline and follow-up on functional performance, as measured with the Katz-15 index
[28].

Both ICERs are subjected to bootstrap analysis and will be presented in cost-effectiveness planes. Deterministic uncertainty will be explored on a range of extremes of parameters potentially influencing the ICERs, i.e. sensitivity analyses. Furthermore, stochastic uncertainty surrounding the ICERs will be presented using a cost-effectiveness acceptability curve.

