In addition to these four key elements, four supporting elements facilitate the care delivery according to the program. First, we developed multidisciplinary practice guidelines on the medical treatment and nursing and social care of eight common geriatric syndromes: depression, dementia, chronic pain, falls, urinary incontinence, malnutrition, and vision and hearing impairment. These guidelines are presented as a job aid in the ZWIP. Second, a practice guideline concerning advance care planning is developed and presented in the ZWIP to promote a proactive dialog between frail elders and their GPs on wishes and expectations regarding medical treatment and end-of-life decisions. Third, procedure agreements regarding easy-access consultation of a geriatrician or a geriatric psychiatrist are constructed. Last, procedure agreements on hospitalization and discharge are made to facilitate the integration of primary- and in-hospital care, thus improving the interdisciplinary continuum of care.

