### Tailored implementation strategies

At baseline, health care professionals in the intervention group are asked for their perceived barriers in the current practice of elderly care as well as for their expectations of the CareWell-primary care program by means of a structured questionnaire. This questionnaire is based on the baseline questionnaire developed in the Dutch Easy Care study
[26] and is pilot tested with peer group professionals. The information thus collected will be used to tailor the implementation strategies and activities, in order to facilitate optimal implementation of the CareWell-primary care program. A combination of implementation strategies and activities targeting both health care professionals and organizations will be used, addressing a variety of barriers for change
[27]: (1) different types of education (tailor-made meetings, coaching on the job, a helpdesk, and expert meetings) to overcome gaps in knowledge, attitude and skills needed to conduct the program, (2) persuasive communication and social influencing by means of large group meetings, in order to enhance both motivation and endurance for participation, (3) provision of additional information through a website, newsletters and written instructions, (4) providing feedback and advice to the participating professionals, and (5) financial reimbursement for all health care professionals and organizations to cover the extra efforts required by the program, to facilitate participation in the intervention. These implementation activities will start nine months before the actual start of the program and will be continued throughout the program.

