**CareWell-primary care program**		
time needed for proactive care planning / case management / multidisciplinary deliberation medication review	-	time registrations by health care professionals

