[46]. Since the participants in the control arm are included with the EasyCare-TOS, it is very well possible this will change their health-seeking behavior. Also, the professionals in the control group might enhance their usual care due to the surplus of information collected with the EasyCare-TOS. However, these possible effects will comparably occur in the participants and professionals of the intervention group. Since we intend to pragmatically study the effects of the CareWell-primary care program in comparison to ‘care as usual’, these facts do not threaten our study as the focus will be on the additional value of our integrated care program in comparison to ‘usual care’, that is conducted following the EasyCare-TOS.

In combining the (cost-) effectiveness study with a thorough process evaluation, we will be able to draw conclusions not merely on the (cost-) effectiveness of the program, but, moreover, on the influence of the degree and process of implementation of the program on its efficacy. Moreover, we will be able to evaluate the feasibility of a nationwide implementation and structural financing of the program within the Dutch health care system.

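### Programme cost is limited to registered professional time and added societal cost to caregivers' lost paid work, so the portal and recurring training have no cost source and unpaid care no stated value

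*Protocol article*

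**What the plan says.** The Economic evaluation section of the protocol article sets a wide scope: "The economic evaluation will be conducted from a societal perspective", and "All relevant direct and indirect costs per participant will be determined by considering costs of the CareWell-primary care program, for the intervention group", together with regular health care costs in both arms.

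It then names the sources. The cost of the programme "will be calculated from the registrations of health care professionals of the time spent on the elements of the program". Table 1 has a single programme row, covering care planning, case management, multidisciplinary deliberation and medication review. Its only source is "time registrations by health care professionals". Beyond regular care, "Societal costs are quantified by calculating productivity losses for informal caregivers who perform paid labor during the study period", using the friction cost method.

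Other sections describe what the programme consumes. The section on the intervention includes the ZWIP portal and, as a supporting element, procedure agreements on "easy-access consultation of a geriatrician or a geriatric psychiatrist". Tailored implementation strategies lists education, on-the-job coaching, a helpdesk and expert meetings, and adds: "These implementation activities will start nine months before the actual start of the program and will be continued throughout the program". Strengths and limitations says that the study will allow a judgement on the "feasibility of a nationwide implementation and structural financing of the program".

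**The concern.** The declared scope is wider than the named cost sources. Some resources that exist only because the programme exists are not professional time on the four listed activities, so a team that follows the text as written has nowhere to enter them. The added societal component records a family's effort only when a caregiver loses paid work.

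Both planned ICERs, per QALY and per Katz-15 difference, use the same cost difference as numerator, so an understated programme cost carries into both. The result is also meant to inform structural financing, and a payer rolling out the programme would have to pay for a portal and for training. The clinical primary outcome is not affected.

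**Working it through.** The article gives no cost, QALY or ICER figure, so there is none to reproduce. The check compares each resource in the text with Table 1 and the Economic evaluation section.

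| Item | Where described | Arm | Stated cost source | Effect on incremental cost |
|---|---|---|---|---|
| ZWIP portal | The intervention; Discussion | Intervention only | None | Understated |
| Education, coaching, helpdesk, expert meetings | Tailored implementation strategies | Intervention only | None | Understated |
| Geriatric and other outpatient consultations | The intervention (supporting elements) | Either arm | No row; the only hospital item is admissions | Unknown |
| Emergency visits | Background, as a possible saving | Either arm | No row | Unknown |
| Unpaid care hours | Not described as a cost | Either arm | No stated valuation | Unknown |
| EasyCare-TOS screening | Study population; Strengths and limitations | Both | None needed for the trial comparison | About zero |
| Reimbursement of professionals | Tailored implementation strategies | Intervention only | Covers extra effort that registered time already values in part | Adding it on top would double count |

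Two sentences in the Economic evaluation section might seem to close the gap. The rule on real cost prices says how to price a resource that has no guideline price, but it adds no resource to the list. The deterministic sensitivity analysis names no parameters and cannot recover quantities that were never collected.

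**How an omission moves the ICER**

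change in ICER = (omitted mean cost per participant, intervention minus control) / (difference in QALYs)

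The QALY gains below are assumptions, as is every euro figure.

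- EUR 100 per participant omitted: 100 / 0.05 = EUR 2,000 per QALY; 100 / 0.02 = EUR 5,000; 100 / 0.01 = EUR 10,000.
- Portal and support at EUR 50,000 to 200,000 in total, over the planned 300 intervention participants: 50,000 / 300 = EUR 167 and 200,000 / 300 = EUR 667 each. The smallest shift is 167 / 0.05, about EUR 3,300 per QALY. The largest is 667 / 0.01, about EUR 66,700 per QALY.
- Screening at equal cost c per participant in both arms: (c − c) / difference in QALYs = 0.

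The width of the second range shows that the documents do not determine the size. They do determine the sign for the portal and the recurring support: a cost borne only by the intervention arm and left out lowers its apparent cost.

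**The case against.** The strongest defence is that this is a condensed article. Table 1 is an overview of sources, the EasyCare-TOS step 2 questionnaire is in an additional file that is not shown, and the caregiver questionnaire is not reproduced. The article says that data on health service use are embedded in EasyCare-TOS. Outpatient contacts, emergency visits or care hours may therefore be recorded. That stands, and it is why those items support only a request to add or clarify. It does not rescue the portal and training, because the text names the source of programme cost, and a fuller costing plan would have to depart from that statement to include them.

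A second defence is that start-up training is a matter of costing choice in a trial ICER. That is fair for the nine-month preparation phase. It is weaker for activities that continue throughout the programme, and no exclusion is stated or justified.

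Three stronger readings are tempting, and the documents do not support them:

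- **Screening is an omitted programme cost.** EasyCare-TOS is used for inclusion in both arms, and Strengths and limitations defines the comparator as usual care following it. Charging it to one arm would itself introduce bias.
- **Most of the omissions fall on the intervention arm, so the ICER as a whole is flattered.** This is shown only for the portal and implementation support. If the programme reduced emergency visits, leaving them out would count against it. Unpaid care could move either way.
- **The plan is really a health-care perspective.** It costs caregivers' productivity losses and domestic care, so that label would be inaccurate.

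**Conclusion.** The point holds in a limited form. The stated cost sources do not deliver the declared societal scope. For the ZWIP portal and the recurring education, coaching and helpdesk, incremental cost is understated by an amount that cannot be computed from the documents; the euro figures above only illustrate how sensitive the ICER is. For unpaid care hours, outpatient consultations and emergency visits, a valuation or a cost row is not stated. The direction of any bias from these is unknown, and the instruments that might capture them are not shown.

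The conclusion assumes that the Economic evaluation section and Table 1 are followed as written. It bears on the economic results and the financing claim, not on the Katz-15 effectiveness analysis.

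**What to change.** 1. Add to Table 1 the portal's running cost and the recurring training, coaching and helpdesk cost. Use project accounts together with the registrations of educational meetings and site visits already planned in Table 2.
2. Put one-off start-up costs in a named scenario. Do not count reimbursement on top of registered time.
3. Add outpatient consultations (including geriatric) and emergency visits in both arms, where EasyCare-TOS records them or can record them.
4. Measure and value informal care hours in both arms through the existing caregiver questionnaire. Otherwise, state that the societal perspective is limited to caregivers' productivity losses and excludes unpaid care.
5. State that EasyCare-TOS screening is common to both arms and stays out of the base-case programme cost. Include it only in a roll-out scenario.

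The cost is slightly more costing work and one or a few questionnaire items, which need to be in place during data collection because care hours are hard to reconstruct afterwards. The programme may look more expensive.

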### Study population

#### Recruitment of general practices

General practitioners (GPs) are recruited to participate in the CareWell-primary care program through an invitational letter and a subsequent telephone call from one of the principal investigators. They are fully informed on the EasyCare Two-step Older persons Screening instrument (EasyCare-TOS)
[23], used to identify the frail elderly study participants, and on the elements of the program. GPs with a minimum of 300 patients aged 70 years or above in their practice population, a solid motivation to implement the program, and the organizational facilities required for implementation are eligible to participate in the intervention arm. After their informed consent, six GPs will be non-randomly assigned to the intervention arm.

A second group of GPs is similarly recruited to participate in the control group. These GPs receive information on the EasyCare-TOS, but no information on the CareWell-primary care program in order to prevent contamination bias. Furthermore, they are explicitly instructed to deliver ‘care as usual’, and not to start new collaborations with community nurses, elderly care physicians or gerontological social workers. No restrictions on existing collaborations are imposed. However, no multidisciplinary team collaborations comparable to those in the CareWell-primary care program are regularly available in usual care. Six GPs consenting to participation are non-randomly assigned to the control arm.

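### The economic evaluation does not carry over the practice level and covariate adjustment of the effectiveness analysis, which leaves the incremental QALY open to baseline utility imbalance

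*Protocol article*

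**What the plan says.** All references are to the Protocol article.

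- **Allocation.** Under Recruitment of general practices, "six GPs will be non-randomly assigned to the intervention arm". The six control practices are also assigned without randomisation.
- **Measurement.** Under Outcome measures and data collection for the cost-effectiveness study, the EQ-5D is taken twice, at baseline and at twelve months.
- **Effectiveness analysis.** The Statistical analysis section of the cost-effectiveness study gives the nesting of patients in practices as its reason for multilevel models. It adds correction for covariates and applies the models to Katz-15 change and all secondary outcomes. The EQ-5D is on the list of secondary outcomes; costs and QALYs are not.
- **Economic analysis.** The Economic evaluation section says that "utilities will be derived using the trapezium rule and the Dutch algorithm", with QALYs calculated from these. For the second ratio, "the ICER will be expressed as the difference in total mean costs weighed against the difference in the sum-scores between baseline and follow-up". On uncertainty, "Both ICERs are subjected to bootstrap analysis and will be presented in cost-effectiveness planes", followed by an acceptability curve and sensitivity analyses over extreme parameter values. The section mentions no practice level, no covariate and no adjustment for baseline utility, and it does not name the unit that is resampled.

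**The concern.** Two safeguards are thought necessary for the clinical outcomes but do not appear in the section that produces the cost-effectiveness results.

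Baseline differences between the arms are foreseeable. Intervention practices must be motivated and suitably organised. Under Informed consent, elders in the intervention arm agree to the screening assessment and the programme, while controls agree to the assessment only. With two EQ-5D measurements, the trapezium rule gives the baseline value half the weight in each patient's QALY. A gap that exists before the programme starts is then counted in the QALY difference unless it is adjusted for.

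Practice may also matter for costs. Programme costs come from time registrations of professionals who work in practice teams, and Strengths and limitations says that delivery is largely unstandardised. If the bootstrap ignores practice, the planes and the acceptability curve will look too certain. The Discussion intends the results to inform nationwide implementation and structural financing.

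**Working it through.** **1. The plan's own figure.** The inputs are in Sample size calculation. For the number of practices, "including 6 clusters in each study-arm is thought to be feasible". For recruitment, the instruction reads "Each general practice is instructed to include 50 frail elderly". The losses it allows for are that "15% of eligible elders will decline informed consent and 20% will be lost to follow-up within the intervention-period of twelve months". From these the article concludes that "the expected cluster size is 35". It also takes ICC 0.01, two-sided alpha 0.05 and power 80%.

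- Cluster size: 50 × 0.85 × 0.80 = 34, stated as 35.
- Design effect: DE = 1 + (35 − 1) × 0.01 = 1.34, with 6 × 35 = 210 patients per arm.
- Detectable effect: (1.960 + 0.842) × √(2 × 1.34 / 210) = 0.316. With 34 per practice (DE 1.33, 204 per arm) it is 0.320.

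The stated 0.32 reproduces. The ICC of 0.01 was assumed for Katz-15 change; the document gives none for costs or QALYs.

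**2. Baseline utility and the QALY.** For a survivor with both measurements, QALY = (U0 + U12)/2 × 1 year. Let the arms differ by d0 in mean utility at baseline. Let a share r of that gap, between 0 and 1, persist to twelve months whatever the programme does. The unadjusted QALY difference then contains

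bias = (d0 + r·d0)/2 = d0(1 + r)/2,

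which is 0.5·d0 when r = 0 and d0 when r = 1. The document gives no utility figures, so d0 is assumed:

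| Assumed d0 | r = 0 | r = 0.5 | r = 1 |
|---|---|---|---|
| 0.02 | 0.010 | 0.015 | 0.020 |
| 0.03 | 0.015 | 0.0225 | 0.030 |
| 0.05 | 0.025 | 0.0375 | 0.050 |

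The Katz-15 ratio has follow-up minus baseline in its denominator, so the baseline gap is subtracted and this mechanism does not arise. Regression to the mean and other confounding may remain there.

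**3. The bootstrap, if patients are resampled without regard to practice.** The true standard error exceeds the naive one by √DE, and a nominal 95% interval covers 2Φ(1.96/√DE) − 1. With 35 per practice:

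| ICC | DE | √DE | Coverage by formula | Simulated, patients resampled | Simulated, practices resampled |
|---|---|---|---|---|---|
| 0.01 (document, Katz-15) | 1.34 | 1.16 | 91% | 90% | 90% |
| 0.05 (assumed) | 2.70 | 1.64 | 77% | 76% | 90% |
| 0.10 (assumed) | 4.40 | 2.10 | 65% | 65% | 90% |

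The simulation used 600 trials of 2 × 6 practices with 35 patients each, a normal outcome, no true difference, and percentile intervals from 400 resamples. Its Monte Carlo standard error near 90% is √(0.90 × 0.10/600), about 1.2 points. The last column shows that resampling six practices per arm, with no further correction, still covers only about 90%. At the document's ICC that is no better than resampling patients.

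**The case against.** The strongest reply is that the Economic evaluation section never describes the method as crude. An adjusted or model-based contrast is also a difference in mean costs, and a bootstrap can be drawn by practice. This is a condensed article, and the resampling unit and the covariates for costs are details that a full analysis plan commonly holds. The multilevel models under Statistical analysis sit within the same cost-effectiveness study, and the EQ-5D is among the outcomes they cover.

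Much of this stands. A reader might infer that both ratios are unadjusted, that the bootstrap is patient-level, and that the uncertainty is therefore understated. The document does not support that. Unadjusted is the natural reading of the cost contrast but is not stated, and the resampling unit is not given, so every coverage figure above is conditional. A reader might also extend the baseline-utility argument to both ratios; it applies to the cost-per-QALY ratio alone. The utility gaps and the ICCs above 0.01 are assumptions, and at 0.01 the loss of coverage is moderate.

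The reply does not dispose of the QALY point. The article fixes the trapezium rule and the two EQ-5D times, and with them the weight that the baseline utility receives. The multilevel models reach the EQ-5D as an outcome, but as written they do not reach costs or QALYs.

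**Conclusion.** The point holds in limited form. The economic evaluation does not carry over the clustering and covariate adjustment that the effectiveness analysis treats as necessary, and the QALY rule it fixes admits baseline imbalance.

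- **Bias.** If the QALY difference is left unadjusted, it contains half to all of any baseline utility gap: 0.01 to 0.05 QALY for an assumed gap of 0.02 to 0.05 with persistence between 0 and 1. The size and direction of any real gap are unknown.
- **Precision.** If patients are resampled without regard to practice, the standard error is understated by about 14% at ICC 0.01 (1 − 1/1.158) and about 39% at an assumed 0.05 (1 − 1/1.643). Coverage is then about 91% and 77%.

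This is a cheap improvement and not a must-fix. The primary Katz-15 analysis is multilevel and covariate-corrected, and is unaffected.

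**What to change.** State the following in the economic analysis before results are seen:

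1. Estimate incremental QALYs by regression adjusted for baseline EQ-5D utility.
2. Adjust incremental costs and QALYs for the same covariates as the effectiveness model.
3. Account for practice, by a multilevel model for costs and QALYs or by a bootstrap that respects practices and has a correction for few clusters. Either route is acceptable. Resampling six practices per arm without correction is not enough, as the simulation shows; a corrected version was not simulated here.
4. Name the resampling unit, and build both cost-effectiveness planes and the acceptability curve from these adjusted, practice-respecting estimates.

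No new data are needed, because baseline EQ-5D is already scheduled. The cost is a little more analysis work and somewhat wider intervals.
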